Otherwise, placement of the ENG-implant is considered safe during breastfeeding and do not presents maternal, neonatal or postpartum risks [11, 13–16]. with no risk of expulsion as occurred with IUC [19].

Also, teenagers presented a high adherence rate when using LARC, with rates of 84 and 74% for the subdermal implant and IUD, respectively [20]. Abnormal uterine bleeding is cited as the main reason for withdrawal of the method [21].

However, a study with women who opted for insertion of the ENG- implant during the immediate postpartum period and followed-up over 3 years, showed that teenagers, who represented 28.2% of the sample, had high continuation rate (94.5%) [22].

The repetition of an UP among teenagers is associated with a low level of schooling, drug addiction and incorrect use of contraceptives among other causes [23]. In this population, the incidence of a new pregnancy within 2 years after the first one was 35%; however, with placement of any LARC at the immediate postpartum period, the rate decreased by 88.2% when compared to non-LARC methods [24].

The aim of our study is to evaluate acceptability, contraceptive efficacy, discontinuation rate by reasons and continuation rates among adolescents who either accept the ENG-implant versus non-acceptors at the immediate postpartum period and follow-up up to one year after placement. In addition, information regarding the relationship between implant use and body composition, pelvic ultrasound characteristics and user satisfaction will be analyzed in both groups.

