## Methods/design

### Study type

A non-randomized and open-label trial.

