### Intervention

Placement of ENG-implant (Implanon NXT, MSD, Oss, The Netherlands) at the immediate postpartum period (up to 48 h after childbearing). This method is not yet offered as routine in the hospital. After properly counselling (including effectiveness, characteristics, possible adverse effects, shelf-life use, and options to change the contraceptive method chosen after enrollment), the participants will be divided in two groups: 1) study group among those who chose ENG-implant and will receive it prior to hospital discharge and 2) non-acceptors of implant and acceptors of other contraceptive methods at the first follow-up between 40 and 60 days postpartum.

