### Sample size

The sample size was calculated based on a prevalence of acceptance of the ENG-implant, based on the satisfaction of teenagers users with the implant [27]. A significance level of 5% and a sampling error (absolute) for the prevalence of 10% were assumed (expected prevalence between 50 and 70%). The formula is based on a binomial distribution (satisfied or not satisfied) n = Z21-a/2 p(1-p) / e2, since e = sampling error of prevalence, p = estimated prevalence (based on literature), a = significance level and Z is the value of normal distribution. The sample size was calculated in *n* = 92,2 and rounded to 100 to contemplate casual lost in the sample. We expected obtaining an estimate of between 50 and 70 teenagers who will accept the method, according to the prevalence and sample error assumed. After collecting the data, the groups will be compared for the dependent variables and the power of the test will be calculated for user satisfaction, method effectiveness, side-effects, body composition, and ultrasound evaluation. The expected flowchart from the study is in Fig. 1.

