### Statistical analysis

The data will be recorded in a data collection sheet prepared for this study. The encrypted data will be stored anonymously in a excel database, after manual review and double typing for descriptive statistical analysis (mean, standard deviation, absolute and relative frequency distribution). The association between independent and dependent variables will be performed using the X^2^test (for qualitative variables) or Fisher’s exact test (when 25% or more of the expected values ​​are less than 5) and through the Student’s *t* test (or the Mann-Whitney test if the data do not present normal distribution, as well as logarithmic, inverse and quadratic transformations of the same). Open questions will be categorized for application of statistical analyzes as well as qualitative variables. Additionally, we will estimated the couple year protection (CYP) which is an indicator of the number of pregnancies averted in each of the groups under evaluation. The level of significance adopted for the statistical tests will be 5%. For statistical analysis, the program Statistical Analysis System (SAS), version 9.4 will be used. Other procedures will be adopted for quality control. Each patient will have an identification number so as not to permit confusion of data, the completed forms will be reviewed and the data put on to the database by two different typists in order to avoid losses and typing errors. All material used for data collection will be stored by the researcher for five years, remaining confidential. This article has followed the SPIRIT guidelines for its elaboration [28].

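### The secondary comparisons set women who chose the implant against women who did not, and every between-group test stated is unadjusted; one short prespecified adjusted analysis would be a cheap improvement.

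*Protocol article*

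**What the plan says.** The Study type section describes "A non-randomized and open-label trial". The Intervention section forms the groups after counselling: a "study group among those who chose ENG-implant and will receive it prior to hospital discharge", and "non-acceptors of implant and acceptors of other contraceptive methods at the first follow-up between 40 and 60 days postpartum".

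The Sample size section rests on the prevalence of implant acceptance (n = 92.2, rounded to 100). It then adds that "the groups will be compared for the dependent variables and the power of the test will be calculated for user satisfaction, method effectiveness, side-effects", and goes on to body composition and ultrasound. The aims at the end of the Background add continuation and discontinuation in acceptors versus non-acceptors.

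The Statistical analysis section names the tests: "The association between independent and dependent variables will be performed using the" chi-square test (Fisher's exact test when expected counts are small) for qualitative variables, and Student's t test "or the Mann-Whitney test if the data do not present normal distribution" for continuous ones. The level is 5%. Couple-years of protection are also estimated by group. The article mentions no regression, stratification, matching, weighting or baseline adjustment.

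The Background also states: "The repetition of an UP among teenagers is associated with a low level of schooling, drug addiction and incorrect use of contraceptives among other causes".

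**The concern.** The two groups differ by a decision that each woman makes. If the factors behind that decision also bear on pregnancy, continuation, satisfaction or body composition, a crude difference mixes the method with the choice. A two-sample test at 5% keeps its error rate for the null of no association between group and outcome. It does not keep it for the null that the implant makes no difference compared with other methods.

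The second null is the one a reader will care about. The aims speak of contraceptive efficacy. The Discussion considers whether implant use changes body composition, and presents the study as reliable evidence on a strategy for reducing unplanned pregnancy. A crude contrast of choosers and non-choosers gives weak support to statements of that kind.

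**Working it through.** **1. The plan's own figure.** n = z² p(1−p)/e² with z = 1.96, e = 0.10 and p = 0.60 (the acceptance expected in the Discussion) gives 3.8415 × 0.24 / 0.01 = 92.2, as stated. At p = 0.50 it gives 96.0 and at p = 0.70 it gives 80.7. This is a precision calculation for a single proportion. Confounding between groups does not enter it, so the acceptance objective stands as planned.

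**2. Group sizes.** From the document: 100 women, 50 to 70 expected to accept. I use 60 versus 40.

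**3. Illustration.** The document gives no imbalance and no outcome risks, so all inputs here are assumed. Suppose the method has no effect. A binary risk factor is present in a proportion a of implant users and b of comparators, and the outcome risk is r1 with the factor and r0 without it.

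- Expected crude risks: p1 = a·r1 + (1−a)·r0 and p2 = b·r1 + (1−b)·r0.
- With p̄ = (60·p1 + 40·p2)/100, the null standard error is s0 = √[p̄(1−p̄)(1/60 + 1/40)], and s1 = √[p1(1−p1)/60 + p2(1−p2)/40].
- Two-sided rejection probability: Φ((|p1−p2| − 1.96·s0)/s1) + Φ((−|p1−p2| − 1.96·s0)/s1).

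| a vs b | r1, r0 | p1 vs p2 | spurious gap | rejection |
|---|---|---|---|---|
| 40% vs 50% | 35%, 20% | 26.0% vs 27.5% | 1.5 points | 5.4% |
| 40% vs 50% | 50%, 20% | 32.0% vs 35.0% | 3 points | 6.2% |
| 35% vs 55% | 40%, 10% | 20.5% vs 26.5% | 6 points | 11.2% |
| 30% vs 60% | 50%, 20% | 29.0% vs 38.0% | 9 points | 15.8% |
| 30% vs 60% | 40%, 10% | 19.0% vs 28.0% | 9 points | 18.9% |

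Worked for the fourth row: p1 = 0.3×0.5 + 0.7×0.2 = 0.29; p2 = 0.6×0.5 + 0.4×0.2 = 0.38; p̄ = (17.4 + 15.2)/100 = 0.326; s0 = 0.0957; s1 = 0.0965. The first term is Φ((0.09 − 0.1875)/0.0965) = Φ(−1.01) ≈ 0.156, and the second adds about 0.002.

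Exact enumeration of the uncorrected chi-square test gives 15.9% for that row. With equal risks of 30% in both groups it gives 5.0%, so the excess comes from the assumed imbalance. Fisher's test lowers the fourth row to 12.8%. Stronger assumptions go higher: 20% vs 60% with risks of 40% and 10% gives 31%.

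**4. How much adjustment the data can carry.** In the fourth row the expected events number 60×0.29 + 40×0.38 = 17.4 + 15.2 = 32.6. Four covariates would leave about 8 events each (32.6/4). For pregnancy, the Background's implant failure rate of 0.4 per 100 women per year implies 60 × 0.004 = 0.24 events in a year among 60 users, so a regression model for pregnancy is not realistic.

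**The case against.** The strongest reply has four parts.

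- **Wording.** The Statistical analysis section speaks of association, and the design is openly labelled non-randomized. A reader might infer that choice-driven differences are going to be reported as effects of the implant. The document does not say so. That reading comes from the aims and the Discussion, and the Discussion's remark on body composition is an expectation of no change, not a reporting rule. This objection stands.
- **Scope.** Acceptance is the lead, sized objective and is untouched. The comparisons are secondary. This also stands and limits the weight of the point.
- **Evidence.** The Background ties schooling, drug use and incorrect contraceptive use to repeat pregnancy, but nothing in the article ties them to choosing the implant, and confounding needs both links. Incorrect use during follow-up is partly how an implant could work, so only use before enrolment is a candidate covariate. Bias is therefore plausible but not demonstrated, and under mild inputs the rejection rate is barely above 5%.
- **A separate analysis plan.** An article may leave adjusted models to one. This stands only in part. The article does fix its inferential tests, down to the Fisher trigger and the transformations to try, and none adjusts. An analysis plan that merely elaborated this section would carry the problem forward.

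**Conclusion.** The point holds for the comparative outcomes: satisfaction, effectiveness, side-effects, body composition, ultrasound, continuation and discontinuation. Groups formed by choice are compared with stated tests that cannot separate method from choice. The acceptance estimate is not affected.

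The size and direction of the bias cannot be obtained from the document. The rejection rates of about 5% to 19% assume no method effect, a 60:40 split and invented imbalances and risks. They show what is possible and do not forecast this trial. Nor does the document support reading the point as a defect of the whole study. It is a cheap improvement to the secondary analyses.

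**What to change.** Amend the Statistical analysis section as follows.

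- For each main comparative outcome with enough events, prespecify one adjusted analysis with a 95% confidence interval, by overlap weighting or a small regression model.
- Use a short list of pre-enrolment covariates, for example age, schooling, prior contraceptive use and drug use. For body composition add the first available measurement. The article schedules bioimpedance at follow-up appointments, so for implant users that value may already follow insertion; say so in the report.
- Show a baseline balance table, and keep the chi-square, Fisher, t and Mann-Whitney results as descriptive.
- Report pregnancy descriptively with exact intervals, because events will be few.
- Word comparative conclusions as associations throughout, including in the Discussion.

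The cost is a paragraph of text, modest programming in the SAS version already named, and making sure the covariates are recorded at enrolment. No more participants are needed. Intervals will be somewhat wider. Unmeasured confounding remains, and so does the different start of follow-up (before discharge for implant users, 40 to 60 days postpartum for the others), which covariate adjustment does not remove. Both should be acknowledged in the report.

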## Discussion

Our expectation is that almost 60% of the adolescents after childbearing at our hospital will choose the ENG-implant as contraceptive method due to the higher contraceptive efficacy when compared to non-LARC methods and few side-effects mainly abnormal uterine bleeding. Breakthrown or unscheduled bleeding after ENG-implant placement is the main reason for early discontinuation; however, we expected that in this particular group of users, due to the physiological bleeding after childbearing, this side-effect could be avoided, they will be satisfy and continuation rate could be high than when placement of ENG-implant occurs at interval period.

In addition, it is unlikely that body composition will be affected with the use of the ENG-implant, because it was described that the weigh gain is almost one kg/year after implant placement, with most patients likely to present normal pelvic characteristics during ultrasound scans.

The large number of UP among Brazilian adolescents and young women is one of the main sexual and reproductive health public problem. One of the consequences is the high cost for the national health service of approximately US$ one billion per year and childbearing at adolescent age contribute significantly to this burden [29]. According to data from the Brazilian Ministry of Health, approximately 20% of all pregnant women are teenagers and, ~ 60% are UP. Therefore, we consider that our study could be a demonstration one to provide reliable data on one strategy about how to reduce these indices.

LARC methods, including the ENG-implant are the first option to reduce UP in teenagers [30]. However, there are few studies in the literature that assess its use in this specific population.

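### Naming Welch's t test for continuous outcomes would protect the 5% level if spread differs between the unequal, self-selected groups (minor, cheap improvement)

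*Protocol article*

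**What the plan says.** The Statistical analysis section of the protocol article tests quantitative outcomes "and through the Student’s *t* test", "or the Mann-Whitney test if the data do not present normal distribution", and also mentions logarithmic, inverse and quadratic transformations. The significance level is 5%. The section does not mention equal or unequal variances.

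Group sizes are not set by design. The study is non-randomized, and the Intervention section forms one group from those who choose the implant and the other from "non-acceptors of implant and acceptors of other contraceptive methods at the first follow-up". The Sample size section says "We expected obtaining an estimate of between 50 and 70 teenagers who will accept the method", from a total of 100. The Discussion expects that "almost 60% of the adolescents after childbearing at our hospital will choose the ENG-implant". The expected split is therefore about 60/40, within a range of 50/50 to 70/30.

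**The concern.** An unqualified reference to Student's t test normally means the version that pools the two variances. That version tolerates unequal variances when the groups are of similar size, but not when they differ in size. Its standard error is then too small if the smaller group is the more variable one, and too large if it is the less variable one. The only trigger for leaving the test is non-normality, so two normal samples with different spreads would still go to it.

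What is at stake is the body-composition and quantitative ultrasound comparisons. The Discussion expects body composition to be unaffected by the implant. A liberal test could contradict that expectation by chance more often than 5% of the time, and a conservative one could miss a real difference.

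**Working it through.** **The plan's own figure.** The Sample size section uses n = Z² p(1 − p)/e², with a "sampling error (absolute) for the prevalence of 10% were assumed". With Z = 1.96, e = 0.10 and p = 0.6 (the midpoint of 50% to 70%), n = 3.8415 × 0.24 / 0.01 = 92.2. This matches: "The sample size was calculated in *n* = 92,2 and rounded to 100 to contemplate casual lost in the sample". The article's calculation therefore rests on 60% acceptance, which gives 60/40 when applied to 100.

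**Inputs.**
- Group sizes 50/50, 60/40 and 70/30 (implant/comparison): Sample size and Discussion sections.
- Level 5%: Statistical analysis section. Two-sided is taken, in line with the Z at 1 − a/2 in the sample size formula.
- SD ratio r (comparison SD divided by implant SD): not in the article; assumed, varied from 0.67 to 1.5.

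**Analytic check.** Set the implant SD to 1 and the comparison SD to r.
- Pooled squared standard error: [(n₁ − 1) + (n₂ − 1)r²]/(n₁ + n₂ − 2) × (1/n₁ + 1/n₂).
- True squared standard error: 1/n₁ + r²/n₂.
- Let q be the square root of pooled over true. The actual level is then approximately 2[1 − Φ(1.96 q)].

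At 60/40 with r = 1.5:
- Pooled: (59 + 39 × 2.25)/98 × (1/60 + 1/40) = 1.4974 × 0.04167 = 0.06239.
- True: 1/60 + 2.25/40 = 0.07292.
- q = √(0.06239/0.07292) = 0.925, so the level is about 7.0%.

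At 70/30 with r = 1.5:
- Pooled: (69 + 29 × 2.25)/98 × (1/70 + 1/30) = 1.3699 × 0.04762 = 0.06523.
- True: 1/70 + 2.25/30 = 0.08929.
- q = 0.855, so the level is about 9.4%.

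At 70/30 with r = 0.67:
- Pooled: (69 + 29 × 0.4489)/98 × 0.04762 = 0.03985.
- True: 1/70 + 0.4489/30 = 0.02925.
- q = 1.167, so the level is about 2.2%.

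**Simulation.** Normal data, equal means, 200,000 replicates per cell. Actual type I error of the equal-variance test:

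| Split | r = 0.67 | r = 0.8 | r = 1 | r = 1.25 | r = 1.5 |
|---|---|---|---|---|---|
| 50/50 | 5.0% | 5.1% | 5.0% | 5.0% | 5.0% |
| 60/40 | 3.5% | 4.1% | 5.0% | 6.1% | 7.0% |
| 70/30 | 2.3% | 3.3% | 5.0% | 7.3% | 9.4% |

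Welch's test stays between about 4.9% and 5.1% in all of these cells. The Mann-Whitney fallback is not a substitute: on the same kind of normal data at 70/30 its level is between 3% and 4% for r = 0.67 and about 7% for r = 1.5.

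**Cost of Welch if the SDs are equal.** Standardised differences of 0.5 to 0.7 are assumed, as the article states none.
- 60/40: up to about 0.2 percentage points of power (82.9% against 82.7% at a difference of 0.6 SD).
- 70/30: about 0.5 to 0.7 points.
- 56/24 (70/30 after an assumed 20% loss): up to about 0.9 points.

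**The case against.** The strongest reply is that nothing in the article shows that the spreads will differ. It gives no SD for any continuous outcome in either group, and with equal SDs the stated test holds 5% at every split. This stands. A reader might infer from the unequal groups that the 5% level fails; the article does not support that.

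A reader might also infer unequal spread, and hence inflation, from the comparison group mixing several methods. That argument is weak. If the SD within each method were the same as in the implant group, a ratio of 1.5 would require method means to vary with an SD of √(1.5² − 1) = 1.12 within-method SDs. That is more than the whole person-to-person spread, and the Discussion expects little effect on body composition. Self-selection could still produce different spreads, but in either direction, so inflation cannot be preferred to conservatism.

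The article never uses the words pooled variance, and an analysis plan that is not shown might name the unequal-variance form. The planned log and inverse transformations may also even out variances in skewed measures such as organ volumes. Both points soften the concern. They do not remove it: the article does name a test, and its only stated reason to depart from it is non-normality.

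Finally, the sample size rests on acceptance, not on a continuous outcome, and several ultrasound items are qualitative and go to the chi-squared or Fisher test. This limits how much depends on the point.

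**Conclusion.** The point holds as a conditional and minor one. The named test has a 5% level that depends on equal spread, in a design whose central expectation is unequal groups formed by choice. At the expected 60/40 split and modest SD ratios the departure is about one percentage point either way. It becomes substantial only when a split near 70/30 coincides with a clear difference in spread.

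These figures rest on assumed SD ratios, normal data, two-sided testing and the reading of Student's t test as the equal-variance form. They support a better choice of test, not a statement that the plan's comparisons are invalid. Neither test deals with confounding from self-selection, which is a separate and larger question for these comparisons.

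**What to change.** In the Statistical analysis section, replace Student's t test by the Welch (Satterthwaite) t test for between-group comparisons of continuous outcomes, applied after any planned transformation. Report the mean difference with its Welch 95% confidence interval. Use it in every such comparison, without a preliminary test of equal variances.

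The change is one line. It needs no further data or participants, and the only downside is the power loss shown above, below about 1 percentage point if the SDs turn out equal.

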## Discussion

Our expectation is that almost 60% of the adolescents after childbearing at our hospital will choose the ENG-implant as contraceptive method due to the higher contraceptive efficacy when compared to non-LARC methods and few side-effects mainly abnormal uterine bleeding. Breakthrown or unscheduled bleeding after ENG-implant placement is the main reason for early discontinuation; however, we expected that in this particular group of users, due to the physiological bleeding after childbearing, this side-effect could be avoided, they will be satisfy and continuation rate could be high than when placement of ENG-implant occurs at interval period.

In addition, it is unlikely that body composition will be affected with the use of the ENG-implant, because it was described that the weigh gain is almost one kg/year after implant placement, with most patients likely to present normal pelvic characteristics during ultrasound scans.

The large number of UP among Brazilian adolescents and young women is one of the main sexual and reproductive health public problem. One of the consequences is the high cost for the national health service of approximately US$ one billion per year and childbearing at adolescent age contribute significantly to this burden [29]. According to data from the Brazilian Ministry of Health, approximately 20% of all pregnant women are teenagers and, ~ 60% are UP. Therefore, we consider that our study could be a demonstration one to provide reliable data on one strategy about how to reduce these indices.

LARC methods, including the ENG-implant are the first option to reduce UP in teenagers [30]. However, there are few studies in the literature that assess its use in this specific population.

